#### Delivery of the Strong Teeth intervention

We will recruit dental teams from 4 to 8 dental practices who will deliver the Strong Teeth intervention as part of the child’s dental check-up and/or at a subsequent visit/s. Each dental team member delivering the Strong Teeth intervention will attend the training outlined above. In addition, parents will receive a toothbrush and guidance on how to use it. For children 0–2 years old, this will be a manual Oral-B toothbrush; for children 3–5 years old, a rechargeable Oral-B electric toothbrush will be provided.

#### Data analysis

The acceptability and feasibility of delivering the Strong Teeth intervention by the dental team will be explored in two ways. First, after delivering each intervention, dental team members will complete a semi-structured diary exploring how the visit went, what oral health barriers were identified, and what Strong Teeth resources were used. Second, having fully completed delivery of the Strong Teeth intervention for all the parents recruited, individual qualitative interviews and/or focus groups with the wider dental practice team will be undertaken. Interviews will be audio recorded, transcribed verbatim, and managed in NVivo. Data will be analysed using framework analysis guided by Ayala and Elder [29] recommendations and the Sekhon, Cartwright [30] theoretical framework of acceptability. This will be coded independently by two researchers, who will then compare codes and resolve any disagreements by discussion [31, 32].

Data regarding progression criteria (see Table 1), including recruitment and retention rates will be used to inform the decision to progress to a definitive trial, with the sample characteristics and overall recruitment and retention data being critical to the trial design.

### Acceptability of the Strong Teeth intervention for parents of children aged 0-5 years old and other outcomes measures

#### Sample size

Twenty parents of children 0–2 years old, and 20 parents of children 3–5 years old will be recruited to the study. The sample size has been derived to satisfy the best practice recommendations of Lancaster, Dodd [33] requiring at least 30 participants and will provide a 95% confidence interval of (74%, 96%) for a minimum anticipated retention rate of 85%. The data from the current feasibility study will inform and modify the sample size calculation for the subsequent definitive trial, although accepting the design (probably involving less home visits), primary outcome (dental decay) and follow-up (3 years) may differ.

Inclusion criteria:
Children 0–5 years old about to visit their general dental practice for a dental check-upChildren attending a general dental practice where the dental team is trained to deliver the Strong Teeth intervention

Exclusion criteria:
Only one sibling can be recruited per householdA parent must be present at the baseline home visit to ensure valid consent

Purposive sampling of parents and children will be undertaken to ensure the sample includes participants from different ethnic groups, living in areas of varying levels of deprivation, and with differing severities of dental decay. However, due to resource restraints, only parents who can understand intervention sessions delivered in English will be included.

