**Methods:**

Forty parents (20 of children aged 0–2 years old, and 20 of children aged 3–5 years old) who are about to attend the dentist for their child’s regular dental check-up will be recruited to the study. Parents and children will be recruited from 4 to 8 different dental practices. In the home setting, consent and baseline oral health behaviour data will be collected. The researchers will ask parents questions about their child’s oral health behaviours, including toothbrushing and diet. Three different proxy objective measures of toothbrushing will be collected and compared with self-report measures of parental supervised toothbrushing (PSB).

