### Feasibility study primary objectives

Using a mixed-methods approach (including self-report questionnaires, dental examinations, filming the toothbrushing interaction between parent and child, and qualitative interviews):
To explore with NHS dental teams, the acceptability and feasibility of delivering the Strong Teeth intervention to parents of children aged 0–5 years oldTo review study findings against progression criteria (see Table 1) and determine whether progression to a definitive trial is appropriate

**Table 1 Tab1:** Progression criteria to definitive trial, without remedial action taken to trial design

Adoption and maintenance of appropriate oral health behaviours at 2–3 month follow-up (≥ 80%) based on self-report measures		
Intervention mechanism produces intended changes in the determinants of oral health behaviour		
Process evaluation	a	Feasibility of delivering the “Strong Teeth” intervention in a dental setting
	b	Intervention, and self-reported and objective outcome measures are acceptable to dental teams and parents
	c	Adequate recruitment (≥ 25%) of eligible families for data collection
	d	Adequate retention (≥ 85%) of consented families to data completion

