### Overall design of the study

In parts of Yorkshire (Bradford, Leeds and surrounding areas) where many children are at high risk of dental caries, 40 parents who are about to attend the dentist for their child’s regular dental check-up (20 parents of children aged 0–2 years old, and 20 parents of children aged 3–5 years old) will be recruited from 4 to 8 different dental practices.

In the home setting, consent and baseline oral health behaviour data will be collected. The researcher will ask parents questions about their children’s oral health behaviours, including toothbrushing [18] and dietary behaviours [19] based on validated measures (the full baseline questionnaire can be found in Additional file 1: Appendix 1). Three different proxy objective measures of PSB will be collected and compared to self-reported parental behaviours: (1) children’s pre-brushing plaque levels per sextant [20]; (2) duration of toothbrushing and parent-child interaction during toothbrushing—the researcher will film the parent/child toothbrushing using a small action camera (GoPro HERO5, GoPro .Inc) and this will be subsequently evaluated by the research team using an established toothbrushing index, please see Additional file 1: Appendix 2 [22]; and (3) toothbrushing activity—parents will be provided with either a paper Magic Timer diary or Disney Magic Timer app for their phone/tablet, which records frequency and duration of toothbrushing. It is imperative to obtain objective as well as self-reported measures of toothbrushing as research has shown there tends to be a mis-match between reported and observed behaviours [23, 24]. The dental team member will also collect the gingivitis rating per sextant [25] and number of teeth present, missing and decayed following training and calibration using British Association for the Study of Community Dentistry (BASCD) standards [26, 27].

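### The (74%, 96%) confidence interval for 85% retention matches a normal-approximation interval that sits too high at n = 40; Wilson gives about 71% to 93%

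*Protocol article*

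**What the plan says.** The Sample size section plans two equal age groups: "Twenty parents of children 0–2 years old, and 20 parents of children 3–5 years old will be recruited to the study". That is 40 families. It supports this number in two ways: a published best-practice recommendation of at least 30 participants, and a precision statement that the sample "will provide a 95% confidence interval of (74%, 96%) for a minimum anticipated retention rate of 85"%. The interval method is not named.

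Table 1, criterion d, uses the same percentage as a progression criterion: "Adequate retention (≥ 85%) of consented families to data completion". No confidence limit enters that criterion. The families "will be recruited from 4 to 8 different dental practices" (Overall design of the study).

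**The concern.** A 95% interval in a sample-size section tells the reader which retention rates the study could exclude if the anticipated rate were observed. The printed interval is symmetric, 11 points either side of 85%. For a proportion near 1 and a sample of 40, the binomial distribution is skewed, and a sound interval reaches further down than up. A symmetric interval then sits too high.

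The lower end is the one that matters more for a feasibility study. The article says that its data will inform the sample size of the definitive trial and that retention data are critical to that trial's design. A reader who takes 74% as the floor consistent with 34 of 40 would be a few points too optimistic.

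**Working it through.** **Inputs.** n = 20 + 20 = 40 and p = 0.85 (Sample size section), so x = 0.85 × 40 = 34 retained. Two-sided 95%, z = 1.96. Families are treated as independent, because the section gives no design effect.

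**Step 1: reproduce the plan's figure (Wald).** p ± z·√(p(1 − p)/n)
- √(0.85 × 0.15 / 40) = √0.0031875 = 0.05646
- 1.96 × 0.05646 = 0.1107
- Interval: 73.9% to 96.1%, which rounds to (74%, 96%).

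The figure is reproduced. The same symmetric formula with a t quantile gives 73.6% to 96.4%, which rounds to the same figures, so the method is inferred only up to that detail. None of the intervals in Steps 2 to 4 rounds to (74%, 96%).

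**Step 2: Wilson interval.** Centre (p + z²/2n)/(1 + z²/n); half-width z·√(p(1 − p)/n + z²/4n²)/(1 + z²/n)
- z² = 3.8415, so z²/n = 0.09604, z²/2n = 0.04802 and z²/4n² = 0.00060
- Centre: 0.89802 / 1.09604 = 0.8193
- Half-width: 1.96 × √(0.0031875 + 0.00060) / 1.09604 = 1.96 × 0.06154 / 1.09604 = 0.1101
- Interval: 70.9% to 92.9%.

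**Step 3: exact (Clopper-Pearson) interval.** The lower limit solves P(X ≥ 34) = 0.025 and the upper limit solves P(X ≤ 34) = 0.025, with X binomial on 40. Interval: 70.2% to 94.3%.

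**Step 4: compare.**

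| Method, 34/40 | Lower | Upper | Width (points) |
|---|---|---|---|
| Wald (matches plan) | 73.9% | 96.1% | 22.1 |
| Wilson | 70.9% | 92.9% | 22.0 |
| Exact | 70.2% | 94.3% | 24.1 |
| Agresti-Coull | 70.5% | 93.3% | 22.8 |
| Jeffreys | 71.7% | 93.5% | 21.8 |

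Against Wilson, the Wald limits are 3.0 points too high at the bottom and 3.1 at the top. Against the exact interval they are 3.8 and 1.8 points too high.

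**Step 5: does 34 of 40 exclude 74%?** Exact binomial probability of 34 or more retained out of 40:
- true rate 74%: 7.5%
- true rate 72%: 4.3%
- true rate 70%: 2.4%

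A 95% lower limit should leave 2.5% in this tail. That happens near 70%, not at 74%.

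**Step 6: coverage of the Wald interval at n = 40.**

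| True retention | Coverage | Interval wholly above truth | Interval wholly below truth |
|---|---|---|---|
| 80% | 90.5% | 7.6% | 1.9% |
| 85% | 93.9% | 4.9% | 1.2% |
| 90% | 91.4% | 8.0% | 0.5% |

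Most misses are in the optimistic direction.

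**The case against.** The strongest reply is that nothing has been miscalculated. The printed limits are correct for the Wald formula, coverage at a true rate of 85% is 93.9%, and the width hardly differs from Wilson's, so the precision that 40 families buy is described about correctly. The sample size also rests on the recommendation of at least 30 participants, and a different interval method would not change it. No decision rule uses the 74%: criterion d is stated without a confidence limit, and the interval that is finally reported will come from the observed data. The definitive trial may also have fewer home visits and a 3-year follow-up, so retention at 2–3 months is only a loose guide to its attrition.

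All of this stands, and it limits the weight of the point. It does not rescue the location of the interval: the section gives readers a lower limit that 34 of 40 would not support.

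A reader might go further and infer three things that the article does not support.
- *That clustering by practice makes the interval materially too narrow.* Families do come from 4 to 8 practices, but the article gives no intra-class correlation, and the follow-up data are collected in the family home. The size of any effect cannot be taken from the document. Stating the independence assumption is enough.
- *That using 85% both as the anticipated rate and as the criterion makes the retention decision a coin toss.* The article calls 85% the minimum anticipated rate. The chance of observing at least 34 of 40 is 0.61 if the true rate is 85%, 0.80 at 88% and 0.90 at 90%. Table 1 is headed as progression without remedial action, so missing 85% is not presented as an automatic stop.
- *That the corrected lower limit should become the floor of an intermediate band in Table 1.* A confidence limit around a hypothetical result reflects sampling error at n = 40. It is not a judgement about what retention is acceptable.

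**Conclusion.** The point holds as a misplaced interval, not as an arithmetic error and not as a flaw in the sample size. For 34 of 40, the stated lower limit of 74% should be about 70% to 71% and the stated upper limit of 96% about 93% to 94%. The overstatement of what can be ruled out applies to the low end only. At the high end the Wald interval excludes less than the alternatives do.

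The conclusion rests on n = 40, on exactly 34 retained, on independent families, and on the inference that a symmetric normal-theory formula was used. The consequence is small: a planning figure that is slightly too favourable, with no decision attached to it.

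**What to change.** In the Sample size section, replace the interval with wording such as: *a 95% confidence interval of about 71% to 93% (Wilson; exact 70% to 94%) for 34 of 40 families retained, assuming that families are independent across practices.* Report the observed retention rate with a Wilson or exact interval as well.

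The cost is one sentence and a slightly less favourable stated lower limit. The number of families, the 85% criterion in Table 1 and the conduct of the study stay as they are.

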### Acceptability to parents/children of the Strong Teeth intervention

The outcome measures and the measurement schedule will be captured through structured questionnaires at baseline, as well as 2 weeks and 2–3 months after the intervention. In addition, qualitative interviews will take place in the parental home at around 3 months after the intervention. An analytical approach using NVivo and theoretical framework analysis will be undertaken, similar to that described for dental teams above.

### Mechanism of action of the Strong Teeth intervention

Qualitative and quantitative data will be used to explore intervention mechanisms with questionnaires and interview topic guides being explicitly developed including questions mapped onto the Theoretical Domains Framework [31], considerate of wider family and community context, as tested and refined through our previous work [11, 12, 17, 21]. The intervention mechanism (i.e. what are the active ingredients within the intervention, and how they are exerting their effect) will be evaluated, and our generic intervention logic model refined [11].

### Adoption and maintenance of appropriate oral health behaviours

Changes in self-report and objective measures of PSB behaviours will be collated. The adoption and maintenance of good oral health behaviours will be measured against national guidance—for example, parental supervised toothbrushing undertaken twice a day with the appropriate amount and strength of fluoride toothpaste [3]. The validity of parent/child reports of PSB behaviours will be compared with three proxy objective measures (1–3, listed in the “Design/methods” section). We will formulate a preliminary measurement model and calculate factor loadings. Factor loadings will be available from the measurement model. By generating a standardised model where the variance of each objective measure is scaled to unity, the associate standardised factor loadings will effectively rank the measures according to the strength of their contributions to PSB. These will be taken as the quantitative assessment for each measure. The same model was used for our HABIT early-phase study and can be seen in Fig. 1 [12]. Other measures of toothbrushing behaviour (such as duration of brushing, amount and strength of fluoride toothpaste used and spitting out toothpaste residue after brushing) will be considered for inclusion in the model.

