**Fig. 1 Fig1:**
[figure not shown]
The measurement (top model) and growth (bottom model) models for the three proxy objective measures of parental supervised toothbrushing (PSB). Published with permission from Eskyte et al. [12]

The dietary data collected at baseline, 2 weeks and 2–3 months will allow changes in dietary behaviour to be evaluated with respect to the frequency of sugary foods and drinks consumed by children. This quantitative dietary data will be used in conjunction with qualitative findings.

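### With at most 40 children, the point order of standardised factor loadings cannot serve as the quantitative assessment of the three objective toothbrushing measures

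*Protocol article*

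**What the plan says.** The section on adoption and maintenance of oral health behaviours first says that the validity of parent and child reports "will be compared with three proxy objective measures". It continues: "We will formulate a preliminary measurement model and calculate factor loadings". The variance of each objective measure is scaled to unity, and "the associate standardised factor loadings will effectively rank the measures according to the strength of their contributions to PSB". The next sentence fixes their role: "These will be taken as the quantitative assessment for each measure". The caption of Fig. 1 describes a measurement model and a growth model for the three proxy measures. Other brushing measures will be considered for inclusion, without commitment.

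On numbers, the Sample size section says: "Twenty parents of children 0–2 years old, and 20 parents of children 3–5 years old will be recruited to the study". The total of 40 is justified by a general recommendation of at least 30 participants and by the precision of the retention rate. Nothing in that section concerns the measurement model.

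**The concern.** The article does more than announce an exploratory fit. It states how the result will be read: the order of the loadings is the assessment of the measures. A standardised loading in a small three-indicator model is a ratio of sample correlations, and such ratios are unstable at n = 40. The solution may not exist in admissible form (a squared loading below 0 or above 1), and when it does exist the order may be wrong. The Discussion presents the lack of robust objective measures of PSB as a key evidence gap that the study will address. A ranking reported without its uncertainty would therefore be read as evidence on that gap.

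**Working it through.** **Inputs from the article.** Three indicators (plaque, filmed brushing, timer diary or app); n = 20 + 20 = 40, with one child per household; 85% retention, so 0.85 × 40 = 34 at follow-up.

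**Inputs assumed.** One common factor, normal data and one visit. The true loadings are not in the article and are varied below.

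**Step 1: the article's own figure.** The only precision statement is that 40 participants "will provide a 95% confidence interval of (74%, 96%) for a minimum anticipated retention rate of 85" per cent. The Wald interval is 0.85 ± 1.96 × √(0.85 × 0.15/40) = 0.739 to 0.961, which reproduces it. It concerns retention only.

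**Step 2: degrees of freedom.** With k indicators on one factor there are k(k+1)/2 variances and covariances and 2k parameters (loadings and residual variances, factor variance fixed). For k = 3 that is 6 − 6 = 0, so there is no test of fit. For k = 4, 5 and 6 the degrees of freedom are 2, 5 and 9.

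**Step 3: why the loadings are unstable.** With k = 3 the solution is closed-form: λ₁² = r₁₂r₁₃/r₂₃, and likewise for the other two. Take true loadings 0.7/0.5/0.3. The true correlations are r₁₂ = 0.35, r₁₃ = 0.21 and r₂₃ = 0.15, and λ₁² = 0.35 × 0.21/0.15 = 0.49. The approximate standard error of r₂₃ at n = 40 is (1 − 0.15²)/√39 = 0.157, as large as r₂₃ itself. If the sample gave r₂₃ = 0.05 with the other two unchanged, λ₁² would be 0.35 × 0.21/0.05 = 1.47, which is inadmissible.

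**Step 4: simulation.** 80,000 datasets per setting. A dataset is inadmissible if r₁₂r₁₃r₂₃ ≤ 0 or any λ² exceeds 1.

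| Assumed loadings | Inadmissible, n = 40 | Admissible and correctly ordered, n = 40 | Same, n = 34 |
|---|---|---|---|
| 0.6/0.5/0.4 | 33% | 18% | 16% |
| 0.7/0.5/0.3 | 42% | 21% | 19% |
| 0.7/0.6/0.5 | 20% | 25% | 23% |
| 0.8/0.6/0.4 | 32% | 32% | 28% |
| 0.8/0.7/0.6 | 12% | 36% | 32% |
| 0.9/0.7/0.5 | 30% | 44% | 39% |
| 0.9/0.8/0.7 | 12% | 51% | 46% |
| 0.95/0.8/0.6 | 31% | 51% | 47% |

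Discarding inadmissible datasets does not rescue the order. Among admissible ones at n = 40 it is right in 36% for 0.7/0.5/0.3, 41% for 0.8/0.7/0.6 and 57% for 0.9/0.8/0.7.

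**Step 5: sample size that would support a ranking.** An 80% chance of an admissible, correctly ordered result needs just over 200 children for 0.8/0.6/0.4, about 400 for 0.7/0.5/0.3 and about 600 for 0.7/0.6/0.5.

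**Step 6: using all three visits.** Pool three visits from 40 children, with an assumed within-child correlation of 0.5. The chance of an inadmissible or misordered result falls to 27–49% for the stronger sets (0.8/0.6/0.4 and above). It stays at 61–89% for the weak and moderate sets (0.4/0.3/0.2 to 0.7/0.6/0.5).

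**The case against.** The strongest reply is that this is a preliminary model serving a secondary objective of a feasibility study. No progression criterion in Table 1 uses the loadings, and the Sample size section expects dental decay to be the definitive trial's primary outcome. That stands. A reader might infer that the study would select a best measure for later trials on this ranking, but the article states no such decision.

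The criterion in Step 4 is also strict, because it asks for all three places right and an admissible solution. Ordering by absolute loading and ignoring admissibility, the full order at n = 40 is right in 40% for 0.7/0.5/0.3 (chance is 1/6, or 17%) and 69% for 0.9/0.7/0.5. The top measure is right in 56% and 78%. So the order carries some information, and calling it pure noise would go too far. It is still not enough for the order alone to be the assessment.

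Four further readings are tempting but not supported:

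- **Fit can never be tested.** Zero degrees of freedom follows only for one factor with three indicators. The text and caption suggest that structure, but Fig. 1 is not shown. A just-identified model is also untestable, which is different from wrong.
- **The two age groups are pooled without adjustment.** The article does not say so. The study brushes are supplied with the intervention, so they cannot affect baseline data.
- **Brushing duration will be counted twice.** Extra measures are only to be considered.
- **The comparison with self-report is missing.** It is stated both in the third secondary objective and in this same section.

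Correlations with self-report are imprecise too. At r = 0.5 and n = 40 the Fisher 95% interval is 0.22 to 0.70. The difference is that a correlation with its interval shows that uncertainty, and a bare ranking hides it.

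**Conclusion.** The concern holds, limited to the rule that the order of the loadings is the assessment of the measures. Across the eight loading sets tabulated, a single-visit analysis of 40 children gives an admissible, correctly ordered result in 18% to 51% of datasets, and in 16% to 47% with 34 children. Inadmissible solutions alone occur in 12% to 42% at n = 40. These rates rest on assumed loadings, normal data and a one-factor, three-indicator structure inferred from the text and caption. Combining visits would reduce the problem, but would not remove it for weak or moderate loadings. The exploratory model itself is not at fault. What the sample cannot support is an unqualified ranking from it.

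**What to change.** Reword the analysis as follows:

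- Describe the measurement model as exploratory. Report each standardised loading with a bootstrap 95% confidence interval, and the bootstrap probability that each measure holds each rank.
- Report inadmissible solutions as such, including how often they occur among the bootstrap samples.
- Remove the statement that the order of the point estimates is the quantitative assessment of the measures.
- Make the correlation of each objective measure with self-reported PSB the main quantitative assessment, with 95% confidence intervals.
- If the final model is one factor with three indicators, say that its fit is not testable.

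This needs a few sentences of analysis text and a little code, with no extra data or visits. The real cost is that the study gives up a definite ranking.
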